### Sample size

Sampling will be carried out throughout the jurisdiction of the 6 de Octubre Health Center, which includes rural, peri-urban and urban areas, with a total potential study population of 3379 children ages 2 to 11 years based on health center databases. Based on this study population of 3379 children aged 2 to 11 years, to measure clinical resistance to albendazole a sample of 380 children was needed. This calculation was made in Epi Info Version 7.2 applying a type I error of 5% and assuming 50% prevalence of helminths in children, 25% frequency of *Trichuris trichiura* in children with helminths, 50% resistance to albendazole based on detection of any helminth in a follow-up sample and adjusting for 10% loss to follow-up for study participants.

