Direct observation: In a properly labeled slide, 0.5 g of feces will be applied with a wooden applicator and 20 µL of saline solution will be added. The first observation will be made from left to right, then the procedure will be repeated with 20 µL of Lugol’s solution added. Both observations will be made with the 10× and 40× objectives in order to qualitatively identify the absence or presence of helminths (*Ascaris lumbricoides*, *Trichuris trichiura*, hookworms, and *Strongyloides stercoralis*).Kato-Katz method: Two grams of feces will be placed on a smooth and sterile surface, covered with a piece of nylon and pressed with a flat-edge plastic applicator. The filtered feces will then be placed in the center of a 41.7 mg template on a slide until the hole is filled, after which the template will be removed and the sample will be covered with a cellophane sheet previously imbued in a glycerol-blue solution of methylene, and pressure will be applied until the sample is distributed homogeneously. After a 30-min incubation, eggs counts will be carried out using the 10× objective and a cell counter, the total number of eggs counts per species will be reported in eggs per gram (epg) and will be multiplied by 24 (41.7 mg template) [27], and the results of each parasite found will be recorded and reported quantitatively. This procedure will be performed on the 4 samples per subject collected throughout the study [28].STH infection by qPCR: To measure the intensity of the infection, quantitative polymerase chain reaction (qPCR) will be used in such a way that the Kato-Katz variability between users is reduced and the sensitivity of the detection of low-grade parasitic infections is increased [29, 30]. Real-time multiplex qPCR will be performed on positive samples (Day 0) for helminths that were identified by direct observation and Kato-Katz for the simultaneous detection of *Ascaris lumbricoides*, *Trichuris trichiura*, *Necator americanus*, *Ancylostoma duodenale*, and *Strongyloides stercoralis* [31]. If the sample from Day 0 is negative, the sample from Day 15 will be analyzed if it is positive for helminths. Amplification will be performed in a Quant Studio 7 Flex thermocycler (Applied biosystems) in a total volume of 25 µL using GoTaq® qPCR Probe Master Mix (Promega, USA) and 5 µL of fecal DNA. There will be two multiplex qPCR assays (STH1 and STH2); STH1 will be used to detect *Ascaris lumbricoides*, *Trichuris trichiura* and *Strongyloides stercoralis*, while STH2 will be used for the 3 species of hookworms. The cycling conditions for both cases will be the following: 1 cycle at 95 °C for 5 min, 40 cycles at 95 °C for 10 s and 1 cycle at 60 °C for 60 s. The primers will be the same ones used by Azzopardi et al. [32] which can be seen in Table 1.**Table 1 Tab1:** Primers used in multiplex qPCR analysis of stool samples by STH1 and STH2

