### Statistical analysis

Data will be analyzed in Access using Stata, using chi square, Fisher’s exact, and Wilcoxon tests to compare frequencies between groups. To analyze the data from direct observation and quantification by the Kato-Katz method, descriptive statistics will be used, to report the prevalence found in percentages. For the sociodemographic and clinical data of the study population, measures of central tendency and dispersion will be used for the quantitative variables and measures of relative frequency for the qualitative variables. Comparisons will also be made between sample 1, sample 2, sample 3 and sample 4 to determine the positivity of each species of parasite found using the Yates chi-square test, setting a significance level of p < 0.05.

The sociodemographic variables will be compared with the parasite load and presence/absence of parasites, using a multiple logistic regression model (univariate t-test), to determine the variables statistically associated with infection by *Ascaris lumbricoides*, *Trichuris trichiura* and hookworms.

The quantification performed with the Kato-Katz method will be compared with the Ct value (Ct threshold) of the multiplex qPCR, by converting Log10 of the absolute egg count per stool sample, in order to estimate the absolute egg counts in eggs per gram (EPG) in the DNA extractions, using the following formula [33]:$${\text{EPG}}\;{\text{Ascaris}} = 10\left( {{\text{Ct}} - 36.97} \right)/ - 3.489,$$$${\text{EPG}}\;{\text{Trichuris}} = 10\left( {{\text{Ct}} - 36.73} \right)/ - 3.288,$$$${\text{EPG}}\;N.\;americanus = 10\left( {{\text{Ct}} - 35.02} \right)/ - 3.641,$$$${\text{EPG}}\;A.\;duodenale = 10\left( {{\text{Ct}} - 35.02} \right)/ - 3.641.$$

To determine treatment efficacy, the prevalence will be measured before and after receiving treatment and compared using the Yates chi-square test. For calculations of cure rate and intensity of infection obtained from qPCR, only data from positive results before taking the first dose will be included [34].

The cure rate will be measured using the following formula:$$\frac{{\# \;{\text{positive}}\;{\text{for}}\;{\text{helminths}}\;\left( {{\text{pretreatment}}} \right) - \# \;{\text{negative}}\;{\text{for}}\;{\text{helminths}}\;\left( {{\text{post}}\;{\text{treatment}}} \right)}}{{\# \;{\text{cases}}\;{\text{positive}}\;{\text{for}}\;{\text{helminths}}\;\left( {{\text{pretreatment}}} \right)}} \times 100.$$

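### Cure and clinical resistance rest on one unconfirmed microscopy reading per visit, so persisting light infections can be recorded as cured, to an extent that depends on baseline egg density

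*Protocol article*

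**What the plan says.** All references are to the protocol article.

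- *Albendazole treatment and clinical follow-up*: one stool before treatment and three afterwards, one per time point. The first follow-up is at 15 to 25 days.
- *Laboratory analysis*: each stool is read by direct smear for presence or absence (0.5 g, saline and then Lugol's) and by one Kato-Katz template. The Kato-Katz count "will be multiplied by 24 (41.7 mg template"), so the smallest non-zero result is one egg, or 24 epg. The article does not state a one-egg limit; it follows from that factor. The same section ranks Kato-Katz as more sensitive than direct microscopy.
- *Sample size*: the calculation assumes "50% resistance to albendazole based on detection of any helminth in a follow-up sample". *Laboratory analysis* likewise equates clinical resistance with helminths detected in the second sample.
- *Laboratory analysis* and the *Abstract*: at follow-up only microscopy-positive specimens go to qPCR. One reason given for qPCR is that "the sensitivity of the detection of low-grade parasitic infections is increased".
- *Statistical analysis*: efficacy is the before/after change in prevalence. Cure is conversion from positive to negative. For cure rate and intensity from qPCR, "only data from positive results before taking the first dose will be included". An egg reduction rate by species is also planned.

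**The concern.** A child counts as infected at day 0 if anything is seen and as cured if nothing is seen at follow-up. Both readings use the same test on a single stool, with no minimum baseline count and no check of a negative. A child with one or two eggs on the first slide can show none on the second with an unchanged worm burden, and more easily still if the drug has cut output without clearing the infection. The assay added for low-grade infection is not applied to the follow-up reading that most needs it.

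Albendazole resistance is a major outcome. If false cure varies with egg density, differences in cure between species, or from other settings, partly reflect intensity rather than drug effect. *Trichuris* is the most exposed: the *Background* cites an egg reduction of only 72.7% in an earlier Peruvian study.

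**Working it through.** **1. The plan's own figure.** Inputs from *Sample size*: a "total potential study population of 3379 children ages 2 to 11 years"; 5% type I error (two-sided assumed); resistance p = 0.50; 10% loss. Precision is not stated; 5 points is assumed.

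n0 = 1.96² × 0.25 / 0.05² = 384.1. With the finite-population correction, n = 384.1 / (1 + 383.1/3379) = 345.0. Then 345 × 1.10 = 379.5, so 380. The total reproduces and does not depend on this point.

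**2. One persisting infection, one slide.** The expected count is m = epg/24. P(no egg) is exp(−m) under Poisson, or 1/(1 + m) under a negative binomial with k = 1. For a 72.7% reduction, multiply m by 0.273.

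| Baseline epg | No effect: Poisson / NB | 72.7% reduction: Poisson / NB |
|---|---|---|
| 24 | 37% / 50% | 76% / 79% |
| 48 | 14% / 33% | 58% / 65% |
| 120 | 0.7% / 17% | 26% / 42% |
| 240 | <0.1% / 9% | 7% / 27% |

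**3. Baseline-positive children, no drug effect.** Assumptions not in the article: true intensity among infected children is gamma with mean μ = 100-500 epg and shape 0.3-1; day-to-day variation is gamma with shape 1, shape 2 or none; eggs are Poisson on 41.7 mg plus an effective smear mass. A child is positive if any egg is seen.

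Simulated false cure with a 4 mg smear is 10-25% at μ = 100, 5-20% at 200 and 2-14% at 500.

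The low ends can be checked by hand. With shape 1, no day-to-day variation and M grams examined, P(negative later | positive first) = 1/(1 + 2Mμ). For M = 0.0457 this gives 1/10.14 = 9.9%, 1/19.28 = 5.2% and 1/46.7 = 2.1%.

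**4. Smear mass.** The article states 0.5 g, not 4 mg. At μ = 200, shape 0.5 and day-to-day shape 2 (the middle scenario), no-effect false cure is about 13%, 9.5% and 3.4% for 4, 40 and 500 mg. The full 500 mg is an upper bound on effective mass, because the article ranks the smear below a 41.7 mg template. Hence about 3-20% at 200 epg: 3.4% is the middle scenario at 500 mg, and 20% is the top of the 4 mg range. Combining 500 mg with the least variation gives 1/(1 + 2 × 0.5417 × 200) = 0.5%, so the lower end is not a floor.

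**5. Uniform 72.7% reduction, no child cleared (middle scenario).** With a 4 mg smear, 32%, 21% and 15% are recorded as cured at 200, 500 and 1000 epg. With a smear as informative as a full Kato-Katz slide the figures are 25%, 16% and 11%. With 500 mg the figure is about 10% at 200 epg.

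**6. Before/after prevalence.** With no drug effect, losses and gains balance: positivity at 200 epg is 72.7% at both visits (its match with the egg reduction figure is a coincidence). Under the 72.7% reduction with a 4 mg smear, prevalence falls by 12-26% in relative terms at 200-1000 epg although no infection has cleared.

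**7. Egg reduction rate, same scenario.** At 100-1000 epg the rate estimated in baseline positives is 73-75% against a true 72.7%, while apparent cure is 15-43%. With no effect, selecting on baseline positives creates a spurious reduction of about 3-15% at 100 epg and 1-9% at 200. Using all children with both samples gives about 0%.

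**The case against.** The case on the other side has several parts, and much of it stands.

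- *The quoted restriction sets no egg threshold and may concern only qPCR measures.* This is correct, and limiting cure to baseline positives is inherent in the measure. The point rests on the sampling, the resistance definition and the qPCR trigger. A qPCR-only reading does not remove it, because follow-up negatives get no qPCR.
- *A reader might infer that resistance is understated overall.* The article does not support that. Any helminth at follow-up counts, so a different species can count. Nor is resistance limited to baseline positives: *Laboratory analysis* provides for a child negative at day 0 and positive at day 15. These push upward. The cure formula as printed also gives the share not cured (100 positive, 80 later negative, gives 20%), so the direction given here applies to the evidently intended cure rate.
- *The before/after prevalence comparison is free of this selection.* That is true with no drug effect, but not under partial reduction (step 6).
- *The size is unanchored.* Baseline intensity is not given, and the effective smear mass matters a good deal. With a 4 mg smear and no effect, false cure is below 5% in most scenarios at 2000 epg. The figures are therefore illustrations.
- *Much of the remedy is planned, and a 5-egg subset is detail for a fuller document.* Species egg reduction is indeed planned, and the 5-egg cut-off has no basis in the article, so it is optional. What remains is that resistance is defined by detection of eggs rather than by egg reduction.

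**Conclusion.** The concern holds in limited form. Among children positive for a species at day 0, the single-stool rule records some persisting or partly reduced infections of that species as cured, more often when infections are light. Under the stated assumptions this is about 3-20% at a mean of 200 epg with no drug effect, and about 10-32% with a uniform 72.7% reduction and nobody cleared. The second range varies smear mass only, so other variation would widen it. The effect is small for heavy infections.

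As a scale for same-species assessment: if half of baseline positives truly stayed infected at unchanged intensity, missing 3-20% of them would turn 50% into 0.50 × 0.97 = 48.5% to 0.50 × 0.80 = 40%. This does not carry over to the any-helminth definition, whose net direction is open. The sample size of 380 is unaffected. This is an inexpensive improvement to the analysis, not a flaw in data collection.

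**What to change.** In *Statistical analysis*:

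1. Assess clinical resistance per species, among children positive for that species at day 0.
2. Base the resistance conclusion on the planned per-species egg reduction rate, computed in baseline positives and also over all children with both samples. Write it as (mean before − mean after) / mean before. As printed, the bracket covers only the numerator: means of 200 and 54.6 epg would give (1 − 54.6)/200 = −26.8% instead of 72.7%.
3. Report the crude cure rate beside it, tabulated by baseline Kato-Katz count, and state that it includes false cures among light infections.
4. Optionally, add cure among children with at least 5 eggs (120 epg) at day 0. In the middle scenario at 200 epg with a 4 mg smear, this cuts no-effect false cure from 12.9% to 3.6% and keeps about 55% of positives. With stronger day-to-day variation it helps less.

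The cost is wording only, with no new samples or assays. The downside is precision. On the plan's assumptions, 380 × 0.90 × 0.50 × 0.25 = 42.75 followed children have *Trichuris*, a 95% half-width of about 15 points at 50%. Keeping 55% leaves about 23.5 and a half-width of 1.96 × √(0.25/23.5) = 20 points. The stratified rates should therefore sit beside the crude rate, not replace it.

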The efficacy of albendazole is variable against *Trichuris trichiura* compared to other anthelmintics; the cure rate ranges between 2.6 and 64.5% [8] and the egg reduction rate ranges between 7 and 83.1%. However, high cure rates of *Trichuris trichiura* are observed in some contexts [9–11]. In a study conducted in the Peruvian Amazon, an open-pair randomized trial was conducted in fifth-grade children from 18 primary schools (9 intervention and 9 control). Intensity of *Ascaris lumbricoides* infection at follow-up was 58% lower in children from intervention schools, a significant reduction as compared to children from control schools (RR = 0.42; 95% CI 0.21 to 0.85), but no significant changes were observed in the intensity of hookworm or *Trichuris trichiura* [12]. In another study from Peru, a total of 1193 school-age children were dewormed with a single dose of Albendazole (400 mg). Of the 909 children who tested positive for at least one STH infection, a random sample of 385 were followed up 2 weeks later with a second stool sample. The efficacy of albendazole was variable, with an egg reduction rate of 99.8% for *Ascaris lumbricoides* (95% CI 99.3–100); 93.6% for hookworm (95% CI 88.2–96.6), and 72.7% for *Trichuris trichiura* (95% CI 58.5–79, 1) [13]. In many cases treatment with albendazole alone appeared inadequate, especially for *Trichuris trichiura*. Other interventions such as combined therapy have been evaluated in other contexts. Ivermectin results in higher cure rates than albendazole and is well tolerated. The benefits of ivermectin for helminth infections would depend on the amount of resistance present [14–16].

Large-scale interventions to control soil-transmitted helminth infections at the community level with anthelmintic drugs such as albendazole have the potential to exert selective pressures which may favor the development of drug resistance, which could significantly reduce the benefits provided by deworming programs. Drug resistance in parasitic nematodes is caused by a single nucleotide polymorphism (SNP) in the β-tubulin gene at codon positions 200 (T → A), 167 (T → A) or 198 (A → C) [17].

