Intensity of infection will be measured using the following formula:$$\frac{{{\text{mean}}\;{\text{egg}}\;{\text{count}}\;\left( {{\text{pretreatment}}} \right) - {\text{mean}}\;{\text{egg}}\;{\text{count}}\;\left( {{\text{post}}\;{\text{treatment}}} \right)}}{{{\text{mean}}\;{\text{egg}}\;{\text{count}}\;\left( {{\text{pretreatment}}} \right)}} \times 100.$$

And the calculation of the rate of reduction of eggs by helminth species:$$\frac{{\left[ {1 - {\text{mean}}\;{\text{egg}}\;{\text{count}}\;{\text{in}}\;{\text{EPG}}\;\left( {{\text{post}}\;{\text{treatment}}} \right)} \right]}}{{{\text{mean}}\;{\text{egg}}\;{\text{count}}\;{\text{in}}\;{\text{EPG}}\;\left( {{\text{pretreatment}}} \right)}} \times 100.$$

In addition, a comparison of the cycle threshold (Ct) by qPCR will be made using the Student’s t-test for paired samples.

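### As printed, the cure-rate formula returns 100% minus the cure rate among children positive at baseline

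*Protocol article*

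**What the plan says.** All of this is in the protocol article.

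- **Statistical analysis, the formula.** After the words "The cure rate will be measured using the following formula", the numerator is the number positive for helminths before treatment minus the number *negative* for helminths after treatment. The denominator is the number of cases positive before treatment, and the ratio is multiplied by 100.
- **Statistical analysis, the sentence just before it.** For the cure rate and for the intensity of infection obtained from qPCR, "only data from positive results before taking the first dose will be included".
- **Statistical analysis, the formula just after it.** Under "Intensity of infection will be measured using the following formula", the numerator is the mean egg count before treatment minus the mean egg count after treatment, so the same quantity stands on both sides of the minus sign.
- **Background.** For albendazole against *Trichuris trichiura*, "the cure rate ranges between 2.6 and 64.5" per cent. Here the term has its ordinary meaning, the share of infected children who clear the infection.
- **Sample size.** The planning assumption is "50% resistance to albendazole based on detection of any helminth in a follow-up sample". Laboratory analysis likewise equates helminths detected in the second sample with clinical resistance.

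No other section defines how the cure rate is calculated.

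**The concern.** A cure rate counts the infected children who become negative. The printed numerator subtracts exactly those children, so what remains is the uncured. A programmer who follows the formula would report a low figure for a drug that works and a high figure for one that does not, under the label *cure rate*. The study is meant to inform the re-evaluation of deworming guidelines (Discussion), and readers will compare its cure rate with published ones, so the direction of this number matters.

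**Working it through.** **Figure to reproduce.** The article states no cure-rate value of its own, so there is none to reproduce. The sample size of 380 does not enter this point. The check is algebra on the printed formula, with the cure rates cited in the Background as test values.

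**Notation.** P = children positive at baseline, all with a post-treatment result. C = those of them who are negative after treatment.

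**Step 1: what the formula returns.**

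- Cure rate in the ordinary sense: C / P × 100.
- Printed formula: (P − C) / P × 100 = 100 − (C / P × 100).

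P − C is the number still positive. The printed value is therefore the proportion still infected, the exact complement of the cure rate.

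**Step 2: numbers.**

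| True cure rate | Source | Printed formula |
|---|---|---|
| 2.6% | Background, lower end for *Trichuris* | 100 − 2.6 = 97.4% |
| 64.5% | Background, upper end for *Trichuris* | 100 − 64.5 = 35.5% |
| 90% | illustrative | 100 − 90 = 10% |
| 50% | complement of the 50% resistance in Sample size | 100 − 50 = 50% |

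The order of the two *Trichuris* values is reversed. The printed and true values agree only at 50%.

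**Step 3: incomplete follow-up.** Suppose 10% of baseline positives have no post-treatment result (the loss assumed in Sample size, applied here to this subset) but stay in P. With c the cure rate among those followed, written as a proportion, the printed value is 1 − 0.9c:

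- c = 0.026: 1 − 0.0234 = 97.7%
- c = 0.645: 1 − 0.5805 = 41.95%
- c = 0.90: 1 − 0.81 = 19.0%

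The lost children are counted as still infected. The result is no longer the exact complement, but it still runs in the wrong direction.

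**Step 4: the one-word repair.** With *positive* in place of *negative*, and everyone followed, P − C children are positive afterwards. The formula becomes [P − (P − C)] / P = C / P, which is the cure rate. This holds only if both counts come from the same baseline-positive children with results. If 10% are lost but kept in P, it gives 1 − 0.9(1 − c). At c = 0.645 that is 1 − 0.9 × 0.355 = 68.05%, which counts the lost children as cured.

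**The case against.** **It is an obvious slip.** The term is used correctly in the Background, and the next formula subtracts like from like, so *negative* was very probably printed for *positive*. An inverted figure would also equal the resistance frequency in the same children, which should be noticed. This stands as an account of how the error arose, and it makes the harm conditional on literal use. It does not make the formula right, and no correct definition appears elsewhere in the article.

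**It is one measure among several.** This also stands. A reader might infer that the study's conclusion on albendazole resistance would be reversed. The documents do not support that. Resistance rests on finding helminths in a follow-up sample (Sample size, Laboratory analysis), and treatment efficacy is also assessed by comparing prevalence before and after treatment. Neither uses the cure-rate formula.

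**The formula could even go negative.** A reader might count every post-treatment negative, including children negative at baseline. For illustration, assume 342 children followed (380 × 0.9), 171 positive at baseline (50%), 86 cured (about half), and all 171 baseline negatives staying negative. Then (171 − 257) / 171 = −50.3%. The sentence before the formula speaks against this, because it confines the cure-rate data to baseline positives. The scenario needs that sentence to cover qPCR results only. The wording leaves slight room for that, since qPCR is named in it. Under that reading the formula would no longer give the proportion still infected, so the two readings are alternatives and cannot be added together. What survives is a request to make the scope of the restriction explicit.

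**A fuller document may have it right.** That may be so, but the objection here is to a formula that the article does print, and prints wrongly.

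**Conclusion.** The formula is wrong as written. Among baseline positives with follow-up results it returns exactly 100% minus the cure rate, so 2.6% and 64.5% become 97.4% and 35.5%. The exactness rests on two conditions: the restriction in the preceding sentence applies, and every child in the denominator has a post-treatment result. With losses left in the denominator the value shifts (35.5% becomes 41.95% at 10% loss), but it is still not the cure rate.

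The consequence is limited. One efficacy measure would be inverted, and only if the formula is applied as printed.

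**What to change.** Replace the formula with:

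- cure rate = (number of children positive at baseline *and* negative at the post-treatment sample) / (number of children positive at baseline with a post-treatment result) × 100.

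Equivalently, change *negative* to *positive* in the numerator, and state that all counts are taken in the same baseline-positive children with a post-treatment result.

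Add a few words to the preceding sentence so that the baseline-positive restriction clearly covers the cure rate from microscopy as well as the one from qPCR.

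The cost is one formula and one clause. Data collection, sample size and the other analyses stay as they are.

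### The printed egg reduction rate is mis-bracketed, the correct formula stands above it under the wrong label, and the Ct-to-EPG conversions lack their exponent

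*Protocol article*

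**What the plan says.** All the formulas are in the Statistical analysis section of the protocol article.

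- **Egg reduction rate.** It is introduced with "And the calculation of the rate of reduction of eggs by helminth species". The numerator of the fraction is a closed bracket that begins "1 - {\text{mean}}\;{\text{egg}}\;{\text{count}}\;{\text{in}}\;{\text{EPG}}\;\left( {{\text{post}}\;{\text{treatment". The denominator is the mean pre-treatment EPG, and the whole is multiplied by 100.
- **Intensity.** Immediately above, the article states "Intensity of infection will be measured using the following formula" and prints (mean pre − mean post) / mean pre × 100.
- **Ct conversion.** The qPCR Ct value is to be compared with Kato-Katz "by converting Log10 of the absolute egg count per stool sample, in order to estimate the absolute egg counts in eggs per gram (EPG". The conversions are then printed as "10\left( {{\text{Ct}} - 36.97} \right)/ - 3.489" for *Ascaris*, "10\left( {{\text{Ct}} - 36.73} \right)/ - 3.288" for *Trichuris* and "10\left( {{\text{Ct}} - 35.02} \right)/ - 3.641" for both hookworm species.

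The Laboratory analysis section uses intensity in a different sense. There it is the infection load, estimated by Kato-Katz in eggs per gram (count × 24) on all four samples, and also by qPCR.

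**The concern.** The article fixes three rules that do not do what their labels say.

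- The egg reduction formula closes its bracket before the division, so it is not a proportion of the baseline count.
- The formula called intensity is a percentage reduction. The section therefore holds two formulas for one quantity, they disagree, and nothing says which governs.
- The conversion lines are linear in Ct, whereas the sentence that introduces them describes a log scale.

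At stake are the species-level egg reductions and any EPG derived from qPCR. If the formulas were programmed as printed, an effective treatment would show a negative or near-zero egg reduction. The qPCR intensities could not be compared with the Kato-Katz counts, although that comparison is the purpose of the conversion.

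**Working it through.** The article states no figure that depends on these formulas, so there is nothing to reproduce. They are evaluated directly.

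**Inputs from the article.** Egg reduction rates of 99.8% (*Ascaris*), 93.6% (hookworm) and 72.7% (*Trichuris*), from an earlier Peruvian study cited in the Background. Kato-Katz multiplier 24 and 40 qPCR cycles (Laboratory analysis). Conversion constants (a, b): 36.97, −3.489; 36.73, −3.288; 35.02, −3.641.

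**Assumed inputs.** Mean pre-treatment EPG of 100 to 5000, and Ct values of 20 to 40. The article gives neither.

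**1. Egg reduction rate**

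Printed: 100 × (1 − post)/pre. Intended: 100 × (1 − post/pre). Expanding the first gives

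printed = true rate − 100 + 100/pre.

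The printed value is therefore too low by 100 − 100/pre percentage points: 99 points at pre = 100, and 99.98 at pre = 5000. Its ceiling, at full clearance, is 100/pre percent.

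| True reduction | Printed, pre = 100 | Printed, pre = 1000 | Printed, pre = 5000 |
|---|---|---|---|
| 100% | 1.0% | 0.1% | 0.02% |
| 99.8% | 0.8% | −0.1% | −0.18% |
| 93.6% | −5.4% | −6.3% | −6.38% |
| 72.7% | −26.3% | −27.2% | −27.28% |
| 0% | −99.0% | −99.9% | −99.98% |

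Example: pre = 1000 and a true 72.7% give post = 273, and (1 − 273)/1000 × 100 = −27.2%.

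The sign turns negative once mean post-treatment EPG passes 1. One counted egg is 24 EPG, so this must happen as soon as more than 1 child in 24 (4.2%) is still Kato-Katz positive for the species.

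**2. The formula labelled intensity**

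(pre − post)/pre = 1 − post/pre, which is the correctly bracketed egg reduction rate. With pre = 1000 and post = 273 it returns 72.7%.

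**3. Ct conversion**

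Printed: 10 × (Ct − a)/b. On the log scale that the text describes: 10^((Ct − a)/b). For *Trichuris* at Ct 25:

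- printed: 10 × (25 − 36.73)/(−3.288) = 35.7 EPG;
- with exponent: 10^3.567 = 3,694 EPG.

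Percentage reductions, using a correctly bracketed rate so that only the conversion differs:

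| Ct change | Conversion | *Ascaris* | *Trichuris* | Hookworm |
|---|---|---|---|---|
| 25 to 30 | printed | 41.8% | 42.6% | 49.9% |
| 25 to 30 | exponent | 96.3% | 97.0% | 95.8% |
| 28 to 33 | printed | 55.7% | 57.3% | 71.2% |
| 28 to 33 | exponent | 96.3% | 97.0% | 95.8% |
| 30 to 38 | printed | 114.8% | 118.9% | 159.4% |
| 30 to 38 | exponent | 99.5% | 99.6% | 99.4% |

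With the exponent, the same five-cycle shift gives the same reduction wherever it starts; as printed, it does not. The printed EPG is negative above Ct 36.97, 36.73 and 35.02 respectively. At Ct 40, the last cycle of the run, it is −8.68, −9.95 and −13.68.

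The slopes point the same way. Read as log10 standard curves, 10^(−1/b) − 1 gives amplification efficiencies of about 93%, 101% and 88%, which are sensible values.

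**The case against.** The strongest reply is that these are typographical slips that would not survive first use. The correct reduction formula is printed one line above the faulty one, the Background cites egg reduction rates in the usual sense, and a rate of 0.1% at full clearance would alert any analyst. That stands as to the likely consequence: a wrong published result is improbable. It does not make the printed rule right, and the reader is still left with two conflicting formulas.

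A second reply is that the exponent may have been a superscript lost when the text was extracted. This cannot be excluded. The equations survive as typesetting code with no power sign and with the division on the base line, so the fault appears to be in the article, but part (3) carries that caveat. The bracket error does not, because it sits explicitly inside the fraction.

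Three stronger readings are tempting, and the article does not support them.

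- *Egg reduction is the main measure of efficacy, so the primary result is at risk.* The major outcomes are resistance and reinfection. The Sample size section takes resistance as finding any helminth in a follow-up sample, and the Statistical analysis section determines efficacy from prevalence before and after treatment.
- *Intensity of infection has no valid definition.* Laboratory analysis already describes it as EPG by Kato-Katz, with qPCR as a further measure. The fault is a wrong label on one formula.
- *The identical constants for the two hookworm species are an error.* Nothing in the article says that a shared curve is wrong, and the source of the constants is not at hand.

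**Conclusion.** The point holds as three errors in printed formulas.

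1. The egg reduction rate is wrong by nearly 100 percentage points for any realistic baseline mean. The size barely depends on the assumed mean: a true 72.7% prints as −26.3% to −27.28% across 100 to 5000 EPG. This is certain from the text.
2. The intensity formula is mislabelled. It is the correct egg reduction rate, and it conflicts both with the formula below it and with the meaning of intensity in Laboratory analysis.
3. The Ct conversions contradict the Log10 description. They yield impossible values (negative EPG, reductions above 100%) within the 40-cycle run. The understatement from about 96–97% to about 42–50% is specific to the assumed change from Ct 25 to Ct 30 and varies with the starting Ct. This part is subject to the superscript caveat and is confined to qPCR-derived EPG. Kato-Katz egg counts and the paired t-test on Ct do not use the conversion.

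No stated sample size depends on any of these formulas, and the before-and-after prevalence comparison does not use them. The correction should nonetheless be made before analysis, because the formulas as stated cannot be applied.

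**What to change.** - Print the egg reduction rate as [1 − (mean post-treatment EPG / mean pre-treatment EPG)] × 100, by species, in children positive for that species at Day 0.
- Relabel the present intensity formula as the egg reduction rate, or delete it as a duplicate. Report intensity as EPG, as Laboratory analysis already describes.
- Print each conversion as EPG = 10^((Ct − a)/b), after checking the published page for a superscript.

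The cost is a text correction. No data collection, sample size or test needs to change.
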